## Abstract

The World Health Organization has documented the impact that a balanced diet has on disease prevention. Overconsumption of meat can lead to obesity, arteriosclerosis, thrombosis, type 2 diabetes and many life-threatening diseases. A new group of proteins has currently emerged in the scientific community of alternative nutrition called “alternative proteins”. Several interventions have been introduced by a large number of healthcare providers in order to promote and enhance people’s dietary habits. Two of the most prevalent models of health-related behaviour modification are the transtheoretical—stages of change—model (TM) and motivational interviewing (MI). The purpose of this study is to research and examine how the ΤΜ and MI could be effectively implemented in the diet of health professionals through alterations of eating habits. The population of the study is to comprise health professionals from «AΤΤΙΚOΝ» University General Hospital, Athens, Greece. The sample of participants is to be selected by the professional environment of the researcher. Participants, through random selection, are to be divided into two groups: the control group, consisting of 50 individuals, and the intervention group, consisting of 50 individuals. The duration of the study is to be from November 2022 to November 2024. The present study is concerned with productive mixed—quantitative and qualitative—evolutionary research along with the application testing of both the ΤΜ and the MI. It is to be conducted specifically on health professionals via self-administered questionnaires and semi-structured interviews.

## 1. Introduction

The world is faced with a major issue of meat overconsumption and its effect on people’s health. In 2017, Americans were reported by the U.S. Department of Agriculture (USDA) to have exceeded the recommended meat consumption levels set by national dietary guidelines [1]. According to a risk factor analysis over the period 2010–2020, the leading causes of mental and physical disabilities, as well as early death, are associated with poor dietary habits in the United States [1]. The positive effect that a plant-based protein diet has had on the prevention of various diseases has been documented through research over the years [1,2]. Recent epidemiological studies from the United States and Europe indicate that overconsumption of red meat—particularly processed meat—is associated with an increased risk of total mortality rate, due to cardiovascular disease, colorectal cancer and type 2 diabetes in the long run for both sexes [2,3]. Owing to the increasing rate of diseases, public health strategies ought to be activated in order to provide quality nutritional dietary behaviours and reduce chronic disease risk.

A great number of interventions has been introduced by a lot of healthcare providers in order to promote and improve people’s dietary habits [4,5]. The ratification of any useful change of habit requires an alternative mindset and, consequently, a modifying behaviour. Plenty of reliable tools are currently available to detect and alter abnormal or dysfunctional behaviour [5,6]. The so-called “cognitive models” aim to examine the factors that contribute to new behavioural adjustment and, thus, a change in dietary approach [7]. Two of the most prevalent models of health-related behaviour modification are the transtheoretical—stages of change—model (TM) and motivational interviewing (MI) [5,6,7,8]. The scientific knowledge obtained is to highly contribute to the advancement and development of health professionals’ health related to the benefits of the alternative protein consumption. Furthermore, the TM and MI use is to be proven auspicious in diet modification.

### 1.1. Alternative Proteins

The global food market and the World Health Organization have been focused on overconsumption of meat and its impact on burdened climate due to human activity, animal abuse, and health issues that humanity is facing nowadays [2]. In the United States and around the world, cardiovascular disease is the leading cause of death. While the risk of developing cardiovascular disease, including heart attack and stroke, increases with age, other risk factors are influenced by lifestyle [1,2]. Certain kinds of behaviour which are known to improve cardiovascular health entail eating healthy food, such as fruit and vegetables, regular physical activity, and controlling high blood pressure, cholesterol and blood sugar levels [2,3]. Consumption of red meat, especially of mammalian origin, such as beef, pork, and lamb, as well as processed meat, which is transformed through salting, curing, fermentation, smoking, or other processes to enhance flavour or preservation, has rapidly been increasing worldwide. These trends can have major negative health and environmental consequences. Rising incomes and urbanization are driving a global dietary transition in which traditional diets are replaced by diets higher in refined sugars, refined fats, oils and meats. By 2050, these dietary trends, if unchecked, would be a major contributor to an estimated 80% increase in global agricultural greenhouse gas emissions from food production and to global land clearing. Global food production emits more than a quarter of all greenhouse gases (GHG), with livestock accounting for more than half of the emissions. Global food production also uses nearly 40% of the Earth’s land as cropland and pastureland. As for freshwater resources, it consumes more than two-thirds of the planetary freshwater from both surface water and groundwater, but it also pollutes water ecosystems with nitrogen and phosphorus. To achieve the goal of creating sustainable dietary systems that provide healthy diets for a growing population but simultaneously reduce environmental impacts, analyses of the quantitative linkages between diets, human and environmental health are of great significance [1,2,3]. Current research shows that there are certain chemicals in red and processed meats—both added and naturally occurring—that cause these foods to be carcinogenic. Considerable evidence from long-term prospective cohort studies has demonstrated that diets high in red and processed meat are associated with increased risk of type 2 diabetes (T2D), cardiovascular disease (CVD) and all-cause mortality [3,9]. The number of companies working on producing meat alternatives is growing worldwide. Recently, a new group of proteins which are called “alternative proteins” has emerged in the world of alternative nutrition. In addition to environmental awareness and economic benefits of consuming alternative proteins, their contribution to human health is very promising [3,9]. Plant-based proteins such as soy, lab-grown meat, single-cell proteins from yeast or algae, and edible insects are some of the alternative proteins [9] which are proven to be a great source of vitamins, fiber, minerals, as well as being low in cholesterol and fat [10,11,12]. Despite their proven nutritional value and the benefits that “alternative proteins” have on human health and environmental awareness, Western consumers reluctantly address them due to established nutritional profiles, lack of information or even increased costs [13,14]. In addition, people’s eating habits are shaped by cultural norms, specifically etiquette on consuming food, which is normally quite challenging to change [15]. The implementation of dietary solutions to the tightly linked diet–environment–health trilemma is a global challenge, and opportunity, of great environmental and public health importance.

### 1.2. The Transtheoretical Model through Stages of Change and the Motivational Interviewing as Interventions to Eating Behaviour Modifications

In the present study, the TM was chosen because of its diversity in relation to other theoretical approaches which aim at behavioural change due to the fact that the behavior modification is interpreted as a sequential processing in this particular model, which involves five stages (Figure 1): 1.2.1. The precontemplation stage: The person does not intend to change behaviour over the next six months. Those involved in this stage have never received information, are poorly informed about the consequences of their behaviour, or feel discouraged due to previous failed attempts.1.2.2. The contemplation stage: The person intends to change their behaviour over the next six months. They are conscious of the advantages and disadvantages of behaviour modification.1.2.3. The stage of preparation: The person intends to take action to modify their behaviour in the immediate future (more specifically, in the period of one month) and they have already formulated an action plan aimed at changing their eating behaviour.1.2.4. The stage of action: The person in this stage has already made modifications regarding their lifestyle within the last six months.1.2.5. The maintenance stage: The individual takes action to avoid the possibility of relapse while feeling progressively more confident about their ability to maintain the behavioural change already achieved [16,17,18,19].

The TM is a theoretical model of behavior change which has been the basis for the development of effective interventions aimed at promoting the change of health-related behaviors. It provides the theoretical framework for understanding the process of behavior modification and MI is the tool that facilitates this modification [16,17]. Progress and stage-change processes can be measured and even small steps of change can be reinforced and the outcome can be assessed [17]. The individual enters the thought process by evaluating the pros and cons associated with this modification. The TM is the theoretical model of behavior change that examines the way that a particular group of individuals behaves towards the problem they are faced with and investigates the possibility of modifying this behavior [18]. The application of the TM has been incorporated into the development of the MI [16]. The main points of MI according to Rollnick and Miller are as follows:Motivation to change is generated by the individual and not imposed by external factors. Motivational interviewing is based on identifying and mobilizing the individual’s internal values and elements in order to change behavior.It is not the therapist’s but the individual’s purpose to clearly and distinctly articulate and resolve their ambivalent feelings. The counselor’s purpose is to enhance the expression of both components of ambivalence and lead the individual to an acceptable resolution of the problem which supports change.Direct persuasion is not an effective method to resolve ambivalent feelings. Such methods have been shown to increase the individual’s resistance and reduce the likelihood of behavior modification.The style of intervention should be calm and eliciting through the counselor’s use of arguments, direct persuasion and aggressive countering.The counselor is direct in helping the individual to examine and resolve their ambivalent feelings.Whether the individual is ready for the desired behavior change will be determined by the interpersonal interaction between the counselor and the patient.The therapeutic relationship isakin to a partnership or companionship [5,7,8,16].

The steps to be followed during the motivational interviewing technique are as follows (Figure 2):Step 1—Engagement

The quality of the therapeutic relationship plays a decisive role on the outcome of treatment.

Step 2—Focus

In this stage, the therapist guides the client to explore a certain path of achievement in order to produce the desired changes.

Step 3—Incitement

At this stage, the therapist promotes the required actions to be followed and helps to overcome any obstacles such as doubt, constant debate and lack of trust.

Step 4—Planning

The last process of motivational interviewing is planning, which involves drawing a strategic plan on ways to achieve the desired change [5,6,7].

The parallel use of these two tools is also articulated by the creators of the MI technique, who argue that the use of the TM offers an understanding of the change process, while the MI offers the tools and all the constructive processes to achieve the modification of deviant behavior [19].

No interventions were found in the literature that modify nutritional behaviors by introducing alternative proteins by applying both the TM and the MI. Therefore, it seems that there is a research gap and an opportunity to study the implementation of these interventions in order to explore the effectiveness regarding nutritional behaviour.

### 1.3. Aim and Objectives of the Study

The purpose of this study is to explore the ways in which the ΤΜ and MI serve as interventions in changing nutritional behavior by introducing alternative proteins to health professionals’ diet.

The objectives of this study are:(i)to investigate the nutritional behavior of the study population regarding the introduction of alternative proteins;(ii)to improve their diet and compliance regarding the introduction of alternative proteins in their diet during their monitoring;(iii)to evaluate the effectiveness of the TM in supporting the modification of health behaviors and assess the intervention program, its design and quality characteristics via the study population after the end of the program;(iv)to compare the effectiveness of a short counseling/information intervention lasting 10 min and a behavior modification intervention with the application of the MI intervention in the form of MET (motivational enhancement therapy) of four sessions of semi-structured interviews and telephone intervention in the study population.

## 2. Methods and Analysis

### 2.1. Design

The present study is concerned with productive mixed—quantitative and qualitative—evolutionary research with application testing of the theory of the TM and MI in a specific case in a special population—health professionals—using self-administered questionnaires and semi-structured interviews.

### 2.2. Ethical Approval

The study protocol has been approved by the scientific board of the «AΤΤΙΚOΝ» University General Hospital, Athens, Greece, on the 7 June 2022 with protocol number 335-25/05/2022, and from University of West Attica, Institutional Review Board Statement, 20-01-23/3159/16-01-23.

### 2.3. Participants and Recruitment

The population of the study will include health professionals from the «AΤΤΙΚOΝ» University General Hospital, Athens, Greece. Healthcare professionals were chosen as the study population because of their daily involvement with patients. Thus, it is believed that if health professionals will be convinced of the nutritional value of alternative proteins, they will be able to educate their patients regarding the outmost health benefits of these products. The sample of participants will be at the professional researchers’ disposal, who will select them. The sample will meet the qualitative criteria that are to be set in order to be included in the study and there will be no additional restrictions regarding demographic, social or other characteristics. Participants will have voluntary participation in the program and free access to it and their data throughout the program. Upon entering the study, they will receive a code number and will be randomized to control or intervention groups via random selection. Participants will also be able to quit at any time they choose without disrupting the process. Participants will be randomly divided into two groups: the control group, consisting of 50 individuals, and the intervention group, consisting of 50 individuals as well. 

#### Exclusion Criteria

The participants who will be excluded from the study and the implementation of the program are those who:Have been diagnosed with mental illness or depression.Do not speak Greek.Have a health problem diagnosed, such as a cardiovascular condition or diabetes.Have an allergy or intolerance to any of the recommended products, such as alternative proteins.Are vegan or vegetarians.Are not healthcare professionals

### 2.4. Nutritional Intervention Based on the Transtheoretical Model and Motivational Interviewing

Two main categories of intervention will be applied to the study population:

#### 2.4.1. Control Group

In the first category of participants, who will be the control group, a program of modification of eating behaviour will be carried out by introducing alternative proteins. Those are to be conducted in the form of a single counselling interview—educational session—of informative character lasting 10 min, during which information is to be provided regarding the importance of diet and alternative proteins. The control group is to complete the classification questionnaire in the stages of change of the ΤΜ both at the beginning and at the end of the intervention. The purpose is to draw conclusions regarding the desire to change their eating habits by intervening according to the statement of desire provided by the tool. 

#### 2.4.2. Intervention Group

A complete program of modification of eating habits is to be carried out in the intervention group according to the principles of the ΤΜ and with the application of the MI, which will be in the form of ME. It will include counselling and support intervention in the form of four semi-structured interviews and telephone interviews lasting 40 min and 10 min, respectively, in total. The intervention group will be evaluated upon completion of the classification questionnaire in the stages of change of the TM, at the beginning and end of the intervention. 

The information concerning the intervention will be made known to the whole population and the distribution of the participants under study. The research is to be conducted between two categories using a randomized method. The participants will not have any information regarding which of the two groups they have joined as well as the differences between the groups—simple blind study—in order to avoid a systematic error during the study [20,21].

Due to ethics, the control team was selected to receive an informative session meeting in order to benefit from the intervention program.

All participants are to receive the same thorough information about the objectives, procedures and benefits of the intervention program in order to be motivated to participate in the same way, as well as ensure anonymity and confidentiality of all personal data and information resulting from their participation in the program, throughout the program and after it. All participants are to receive separate forms:Information and mobilization form concerning the intervention program, research that will be carried out, goals, procedures and expected benefits from their participation.Signed consent form before joining the program.Complaint form.

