A.A 10-min interview will have an educational and advisory character and will not follow any other specific methodological scheme. It is to concern the category of the population/control group.B.There are to be four 40-min interviews/meetings with 10-min intermediate telephone interviews according to the methodology of motivational enhancement therapy (MET) [16,17,18,19]. The interviews are to be held every 15 days with an intermediate telephone interview that will be determined in agreement with each participant and will aim to monitor and evaluate the effort to modify the behaviour of the participants and provide brief advice on issues that may arise.

The principles and techniques of motivational interviewing will be applied in order to support the mobilization of the individual to follow changes in their behaviour through the resolving of ambivalence, method of ejection and empowerment of self-efficacy, and the management of the individual’s resistance to change through empathetic dialectic [16,17,18,19].

4.Questionnaire for the evaluation of attitudes, acceptance and willingness of consumers to pay for innovative products [22,23].

The questionnaire will be provided at the beginning and at the end of the process to both groups of participants and will aim to record the change in the behaviour of participants—consumers towards innovative products such as alternative proteins. This questionnaire has been created and weighed in the context of a graduate study conducted by a student of the Agricultural University of Athens, Department of Rural Economics and Development, in order to record the attitude, acceptance and willingness of consumers to pay for innovative products. For the present study, written permission has been obtained by the author for its use [23]. 

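### The article claims participant blinding, but its own disclosure sentences and the visible difference between the programmes mean that this claim cannot be relied on to protect self-reported outcomes

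*Protocol article*

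**What the plan says.** All the blinding statements are in section 2.4.2 of the protocol article.

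- **The claim.** "The participants will not have any information regarding which of the two groups they have joined as well as the differences between the groups". The article labels this a simple blind study and gives its purpose: "in order to avoid a systematic error during the study".
- **Disclosure to everyone.** Shortly before, the section says: "The information concerning the intervention will be made known to the whole population and the distribution of the participants under study". Shortly after, it says: "All participants are to receive the same thorough information about the objectives, procedures and benefits of the intervention program". Each participant also receives a written form, described as: "Information and mobilization form concerning the intervention program, research that will be carried out, goals, procedures and expected benefits from their participation".

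The two programmes are described elsewhere as follows.

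- **Control (section 2.4.1):** a "single counselling interview—educational session—of informative character lasting 10 min".
- **Intervention (section 2.5, item 3B):** "There are to be four 40-min interviews/meetings with 10-min intermediate telephone interviews", held 15 days apart. Section 2.4.2 words the durations differently: "four semi-structured interviews and telephone interviews lasting 40 min and 10 min, respectively, in total".
- **Both arms (section 2.5, item 3):** a common 30-minute preparatory interview.

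Outcomes come from self-administered questionnaires and interviews (section 2.1). They are self-declared stage of change (section 2.5, item 2) and attitudes and willingness to pay (section 2.5, item 4). Participants are staff of one hospital, drawn from the researcher's professional environment (Abstract, section 2.3).

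**The concern.** The article presents blinding as its safeguard against systematic error. A person who has been told the procedures of the intervention programme, and who then attends either one short session or a series of interviews with calls between them, is well placed to work out which arm they are in. Colleagues in one hospital can also compare what they received.

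This matters because the outcomes are what participants say about their own intentions and attitudes. If people in the intensive arm know that they are in it, and know the benefits expected of it, they may report more progress than they have made. Any excess over the control arm adds directly to the between-arm difference that objective (iv) sets out to measure. The Conclusions section already expects a statistically significant advantage for the intervention. A reader told that the study was blinded would discount this source of error when they should not.

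**Working it through.** **1. Is there a stated figure to reproduce?** No. The article attaches no effect size, power or bias allowance to the blinding claim. The check is therefore a comparison of its own statements, followed by an illustration of scale.

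**2. What is withheld against what is disclosed (section 2.4.2).**

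| Said to be withheld | Said to be disclosed to all |
|---|---|
| Which group the participant joined | Information on the intervention and, in an unclear sentence, the distribution of participants |
| How the groups differ | Objectives, procedures and benefits of the programme, repeated in a written form |

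Knowing the procedures of the intervention programme goes a long way towards knowing how the groups differ. The two columns cannot both stand without a statement of what exactly is held back.

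**3. How different are the programmes?** Arm-specific contact time, leaving out the common 30-minute interview:

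- Control: 1 × 10 = 10 min.
- Intervention, section 2.5: 4 × 40 = 160 min face to face. With 3 or 4 ten-minute calls (the number is an assumption), 190–200 min. The ratio to control is 16 without calls and 19–20 with them.
- Intervention, section 2.4.2, if its wording means totals: 40 + 10 = 50 min, a ratio of 5.

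On either reading it is four interviews plus calls against one session. Section 2.5 also has the intervention arm repeat the stage questionnaire at the start of each session, while controls complete it only at the beginning and end. The article describes no control programme matched for attention.

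**4. Scale, as an illustration only.** From the article: 50 per arm (section 2.3) and a chi-squared or Fisher test (section 3.4). Assumed: a binary outcome such as forward movement in stage, no true effect, a two-sided 5% level, a control rate p₁ of 20–50%, and a net over-reporting shift d in the intervention arm, so that p₂ = p₁ + d.

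With p̄ = (p₁ + p₂)/2, s₀ = √[2p̄(1 − p̄)/n] and s₁ = √[p₁(1 − p₁)/n + p₂(1 − p₂)/n], the chance of a significant result is

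1 − Φ[(1.96·s₀ − d)/s₁] + Φ[(−1.96·s₀ − d)/s₁].

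Example with p₁ = 0.20 and d = 0.15:

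- p̄ = 0.275
- s₀ = √(2 × 0.275 × 0.725/50) = 0.0893
- s₁ = √[(0.16 + 0.2275)/50] = 0.0880
- The first argument is (0.1750 − 0.15)/0.0880 = 0.284, so the rate is 1 − Φ(0.284) = 0.388. The other tail is negligible.

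| Net shift d | p₁ = 20% | 30% | 40% | 50% |
|---|---|---|---|---|
| 0 | 5.0% | 5.0% | 5.0% | 5.0% |
| 5 points | 9.2% | 8.3% | 7.9% | 7.9% |
| 10 points | 21.0% | 18.1% | 17.0% | 17.0% |
| 15 points | 38.8% | 33.9% | 32.2% | 32.7% |
| 20 points | 59.0% | 53.3% | 51.6% | 53.3% |

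**The case against.** The strongest defence is that a participant sees only one programme. Both arms start with the same preparatory interview, and section 2.4.1 describes the control session too as a programme for modifying eating behaviour. Someone who is never told about the other arm need not know that theirs is the lesser one. This stands in part: unblinding is likely but not certain. It does not rescue the claim, because the article promises all participants the programme's procedures and places them in one workplace.

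Four stronger readings are tempting, and the documents do not support them.

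- **That each person's allocation is announced.** The sentence on the distribution of participants is garbled. It may mean only that people will be told they are to be divided into groups.
- **That the counsellors are the participants' colleagues and also collect the outcomes.** The article says that participants come from the researcher's professional environment. It does not say who conducts the interviews or who receives the questionnaires.
- **That all the reporting bias is due to failed blinding.** Some over-reporting could follow from repeated counselling itself, even if participants never learned of the other arm. Changing the label would not remove it.
- **That a particular inflation can be quoted.** A move from 20% to 35% gives an odds ratio of (0.35/0.65)/(0.20/0.80) = 2.15, but neither the rate nor the shift is in the article. Controls also receive counselling and a motivating form and may over-report too, so only the net difference counts. At a 5-point net shift the effect is modest.

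Form-return logistics and masked analysis may also be covered in a fuller protocol. Their absence from a journal article is not held against it here.

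**Conclusion.** The concern holds in a limited form. The article states a design property, participant blinding as protection against systematic error, that its own disclosure sentences and programmes do not support. That protection cannot be relied on for the self-reported comparison. It does not follow that blinding will fail for every participant, or that the result will be biased by a known amount.

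The false-positive rates above, from about 8% at a 5-point net shift to 59% at 20 points, rest wholly on assumed shifts and control rates and on treating the outcome as binary. They show that at this sample size even moderate differential reporting could produce a significant result without a true effect.

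An open-label behavioural trial is acceptable. What should be corrected is the claim that it is blinded.

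**What to change.** 1. In section 2.4.2, remove the simple-blind claim and describe the trial as open-label to participants. Alternatively, state exactly what is withheld, for example the study hypothesis. In either case, make the disclosure sentences and the information form agree. Withholding the hypothesis would mean revising a form that now sets out goals and expected benefits.
2. Rewrite the sentence on the distribution of participants so that it says whether individual allocation is disclosed.
3. Reconcile the session durations in sections 2.4.2 and 2.5.
4. Have baseline questionnaires completed before allocation is disclosed.
5. Have end questionnaires returned under the code number already assigned at entry (section 2.3), and not to the counsellor. This reduces the pressure to please but does not abolish it.
6. Run the between-arm comparison on masked arm codes. This does not address self-report, but it is useful because section 3.3 leaves the choice of techniques to the researcher after the descriptive results are seen.
7. State differential self-report as a limit on the conclusion.

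The cost is some rewording, a small change in how existing forms are returned, and a less favourable design label. Sample size and visits are unaffected.
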